## Abstract

**Background:**

Multiple pregnancies are at high risk for preterm birth, and therefore an important cause of infant mortality and morbidity. A pessary is a simple and potentially effective measure for the prevention of preterm birth. Small studies have indicated its effectiveness, but large studies with sufficient power on the subject are lacking. Despite this lack of evidence, the treatment is at present applied by some gynaecologists in The Netherlands.

**Methods/Design:**

We aim to investigate the hypothesis that prophylactic use of a cervical pessary will be effective in the prevention of preterm delivery and the neonatal mortality and morbidity resulting from preterm delivery in multiple pregnancy. We will evaluate the costs and effects of this intervention. At study entry, cervical length will be measured. Eligible women will be randomly allocated to receive either a cervical pessary or no intervention. The cervical pessary will be placed in situ at 16 to 20 weeks, and will stay in situ up to 36 weeks gestation or until delivery, whatever comes first.

The primary outcome is composite bad neonatal condition (perinatal death or severe morbidity). Secondary outcome measures are time to delivery, preterm birth rate before 32 and 37 weeks, days of admission in neonatal intensive care unit, maternal morbidity, maternal admission days for preterm labour and costs. We need to include 660 women to indicate a reduction in bad neonatal outcome from 7.2% without to 3.9% with a cervical pessary, using a two-sided test with an alpha of 0.05 and a power of 0.80.

**Discussion:**

This trial will provide evidence on whether a cervical pessary will decrease the incidence of early preterm birth and its concomitant bad neonatal outcome in multiple pregnancies.

**Trial registration:**

Current Controlled Trials: NTR 1858

## Background

Twin pregnancies are at high risk for preterm birth. In The Netherlands 15% of the women with a multiple pregnancy deliver before 34 weeks of gestation[1]. About 1 in 60 pregnancies is a twin pregnancy, and about 30% of the preterm born children admitted in a neonatal care (NICU) are from twin pregnancies. [2,3]. The incidence of twin pregnancies remains high due to an increase in the age of pregnant women. Prevention of preterm birth is therefore a major goal of obstetric care. However, strategies to prevent preterm birth have been largely unsuccessful.

Bad neonatal outcome includes respiratory distress syndrome (RDS), bronchopulmonary dysplasia (BPD), intraventricular haemorrhage (IVH), periventricular leucomalacia (PVL), necrotizing enterocolitis (NEC), sepsis and death before discharge [4]. The prevalence of this poor neonatal outcome is 77%, 35% and 12% in children born after early preterm delivery between 24-27, 28-32 and 32-34 weeks, respectively [3]. But after 34 weeks this incidence sharply declines to less than 2% at term. The probability that a woman with a multiple pregnancy delivers at these gestational ages is 1.8%, 5.4% and 7.2%, respectively [2].

In total, about 8% of the multiple pregnancies will result in the death of at least one child, whereas in 7% of the pregnancies at least one of the children will remain severely disabled. Moreover, another 20% of the pregnancies results in a moderate handicap of at least one of the children.

The cost of these poor outcome is enormous. About 500 of these children will be admitted into a neonatal intensive care unit at a cost of € 1500,- per day, with an average duration of admission of 10 days. This results in a total cost of 16 million euro per year from the birth of 1.000 children before 34 weeks.

A pessary is a simple and potentially effective measure for the prevention of preterm birth.

Preliminary evidence on the effectiveness of a pessary to prevent preterm labour is promising. Various designs of pessary have been used[5] but none has been evaluated in a well-designed randomised trial. In the only randomised controlled trial of pessary prophylaxis comparing pessary to cerclage [6], the type of pessary used and the study methodology were not well described. A double ring shaped pessary is at present the most popular pessary, and widely used in The Netherlands and Germany with the manufacturers selling around 2000 per year.

The first reports show a strong beneficial effect of a pessary in women with singleton pregnancies and a short cervix [7]. A cohort study in twins showed that a pessary prolonged pregnancy and decreased delivery before 32 weeks [8]. A prospective cohort study by Acharya et al. also used an double ring shaped pessary (Arabin-pessary) to treat cervical incompetence in women with a cervical length ≤ 25 mm, before 30 weeks [9]. This study showed that in 55 percent of the patients, the pregnancy could be postponed to 34 weeks or more. In view of these data, we will set up a randomised clinical trial on the subject. The aim of this trial is to investigate whether a prophylactic cervical pessary will lower the incidence of neonatal morbidity by reducing the number of preterm births in multiple pregnancy.

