### Outcome measures

The main outcome parameter is the composite morbidity rate of children in the two groups. This composite morbidity rate contains the following variables: periventricular leukomalacia (PVL), severe Respiratory Distress Syndrome (RDS), Broncho Pulmonal Dysplasia (BPD), Intraventricular Haemorrhage II B or worse, Necrotizing Enterocolitis (NEC), proven sepsis and death before discharge from the nursery 24. They will be measured until 6 weeks after the expected term date of delivery.

Secondary outcome measures are time to delivery, preterm birth rate before 32 and 37 weeks, days of admission in neonatal intensive care unit, maternal morbidity, maternal admission days for preterm labour and costs. At present, a longer follow-up is not planned.

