### Statistical issues

#### Sample size

The sample size is calculated based on the primary outcome 'bad neonatal outcome'. In the control group, 'bad neonatal outcome' is expected in 7.2% of the children (1.8%*77% + 5.4%*35% + 7.2%*12% + 35.6%*8% + 50%*.5% = 7.2%). In this calculation, the first rate represents the probability that a patient delivers at that gestational age, whereas the second rate represents the probability of 'bad neonatal outcome' at that particular gestational age. In case of treatment, 'bad neonatal outcome' is then expected in 3.9% of the children (0.9%*77% + 2.7%*35% + 3.6%*12% + 17.8%*8% + 75%*.5% = 3.9%).

Because the outcomes in children from multiple pregnancies are to a certain extent non-independent, we adjusted our sample size assuming a correlation of 0.6 for composite neonatal morbidity between two children born from the same pregnancy[11]. Using a two-sided test with an alpha of 0.05 and a power of 0.80 we need 330 women in the control group and 330 in the intervention group (total of 660 women).

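### As worded, three of the five planning event rates belong to a broader composite than the primary outcome, so 7.2% v 3.9% may be too high; the definitions need reconciling

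*Protocol article*

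**What the plan says.** The Background defines the composite: "Bad neonatal outcome includes respiratory distress syndrome (RDS), bronchopulmonary dysplasia (BPD), intraventricular haemorrhage (IVH), periventricular leucomalacia (PVL), necrotizing enterocolitis (NEC), sepsis", plus death before discharge. None of the components carries a severity or proof requirement. The next sentence attaches rates to that composite: "The prevalence of this poor neonatal outcome is 77%, 35% and 12% in children born after early preterm delivery between 24-27, 28-32 and 32-34 weeks".

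Outcome measures lists the same seven conditions as the main outcome but restricts three of them: "severe Respiratory Distress Syndrome (RDS), Broncho Pulmonal Dysplasia (BPD), Intraventricular Haemorrhage II B or worse, Necrotizing Enterocolitis (NEC), proven sepsis". The abstract agrees with the restricted version: "The primary outcome is composite bad neonatal condition (perinatal death or severe morbidity").

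The Sample size section says that it is based on the primary outcome, and continues: "In the control group, 'bad neonatal outcome' is expected in 7.2% of the children". It obtains this figure by weighting five gestational-age-specific rates: 77%, 35%, 12%, 8% and 0.5%. The first three are the Background rates, unchanged. The 8% and 0.5% are printed only here, with no source or definition. The Background says only that the incidence falls sharply after 34 weeks, to under 2% at term. The article does not say that any rate was adjusted to the stricter definition.

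**The concern.** Taken as worded, the two definitions are nested. Every child with severe RDS, IVH IIB or worse, or proven sepsis is also an event under the Background list, but not the reverse. A child whose only problem is milder RDS, a lower-grade IVH or unproven sepsis would count in the planning rates and not in the trial. The rate of the restricted composite can therefore only be equal or lower.

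For a fixed relative effect, a lower event rate means less power. The 7.2% and 3.9% are the trial's main planning figures and appear in the abstract. If they describe a wider endpoint than the one analysed, a null result would be read against more power than the trial has.

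**Working it through.** **1. The planning rates (inputs from Sample size).**

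- Control: 1.8%×77% + 5.4%×35% + 7.2%×12% + 35.6%×8% + 50%×0.5% = 1.386 + 1.890 + 0.864 + 2.848 + 0.250 = 7.24%.
- Pessary: 0.9%×77% + 2.7%×35% + 3.6%×12% + 17.8%×8% + 75%×0.5% = 0.693 + 0.945 + 0.432 + 1.424 + 0.375 = 3.87%.

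The stated 7.2% and 3.9% reproduce. The three Background rates supply 4.14 of the 7.24 control points and 2.07 of the 3.87 pessary points. The 8% and 0.5% strata supply 3.10 and 1.80.

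**2. The stated sample size.** Children per arm, two-sided alpha 0.05, power 0.80:

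n = [1.96√(2p̄(1−p̄)) + 0.8416√(p1(1−p1)+p2(1−p2))]² / (p1−p2)²

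With p1 = 0.072, p2 = 0.039, p̄ = 0.0555: (1.96×0.3238 + 0.8416×0.3230)² / 0.033² = 754.4, or 755 rounded up. With two children per woman and correlation 0.6, the design effect is 1 + (2−1)×0.6 = 1.6. That gives 755×1.6/2 = 604 women per arm, so the stated 330 does not reproduce.

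Power is Φ{[(p1−p2)√n − 1.96√(2p̄(1−p̄))] / √(p1(1−p1)+p2(1−p2))}. For 330 women per arm the effective n is 330×2/1.6 = 412.5 children, and power is Φ{(0.6702 − 0.6346)/0.3230} = Φ(0.110), about 54%.

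**3. The effect of a narrower endpoint.** The documents give no rates for the restricted composite. Let s be the share of planned events that meet it (an assumption), the same at every gestational age and in both arms, with the planned shifts between strata kept. There are two versions:

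- A scales all five strata: 7.2%×s v 3.9%×s.
- B scales only the three strata named in the Background: (4.14×s + 3.10)% v (2.07×s + 1.80)%.

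| s | Version | Control v pessary | Power, 754 independent children per arm | Power, 330 women per arm, correlation 0.6 |
|---|---|---|---|---|
| 1.0 | stated rates | 7.2% v 3.9% | 80% | 54% |
| 0.9 | A | 6.5% v 3.5% | 75% | 50% |
| 0.9 | B | 6.8% v 3.7% | 79% | 53% |
| 0.7 | A | 5.0% v 2.7% | 64% | 40% |
| 0.7 | B | 6.0% v 3.2% | 72% | 47% |
| 0.5 | A | 3.6% v 1.95% | 50% | 30% |
| 0.5 | B | 5.2% v 2.8% | 64% | 40% |

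Version B is built from the unrounded sums. At s = 1 these (7.24% v 3.87%) give about 82% and 56% by the same formula, so the loss under B is measured from there.

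The first power column isolates the endpoint question in a sample that would have 80% power. The second is the trial as sized. Under version A, the independent children per arm needed for 80% power rise from 754 to 843, 1,097 and 1,554 at s = 0.9, 0.7 and 0.5.

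**The case against.** The strongest reply is that the Background is introductory prose in a condensed article. It names the same seven conditions as Outcome measures, and leaving out the grades may be shorthand. The Sample size section calls its endpoint the primary outcome, and the abstract describes that outcome as death or severe morbidity. On this reading the rates already match the restricted definition, and the defect is one of wording with no effect on power. The sources cited for the component list and for the rates are not at hand, so this cannot be excluded. A reader might infer that the rates certainly come from a composite counting RDS, IVH or sepsis of every grade. The documents do not support that, because it rests only on missing qualifiers.

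Second, only three of the five rates trace to the Background definition. Scaling the whole 7.2% and 3.9% assumes something about the 8% and 0.5% that the text does not say. This stands, and it is why a range is given.

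Third, a reader might infer that the stated 80% power is correct for the broader endpoint and wrong only for the narrower one. That does not hold. The stated inputs give about 54% at 7.2% v 3.9%, so the 80% belongs to neither endpoint.

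What survives is that two printed definitions differ, one set of rates serves both, and at least one section needs correcting on either reading.

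**Conclusion.** The point holds as an unreconciled mismatch between Background, Outcome measures and Sample size. Overstatement of 7.2% v 3.9% is likely on the text but not proven, and its size is unknown.

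If it is real, the loss depends on s and on which strata it touches. In a sample with about 80% power, little is lost at s = 0.9 if only the three Background strata shrink; at s = 0.7 or below the loss is material on either version. In the trial as sized, the loss would come on top of power that is already about 54%. That shortfall is a separate matter of the clustering arithmetic and does not depend on this point.

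The figures assume twins throughout, no dropout, a constant s and the planned stratum shifts. The correction is worth making because the trial relies on these rates and the repair is cheap.

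**What to change.** Reconcile Background, Outcome measures and Sample size to one definition. State which definition each of the five stratum rates follows, with a source for the 8% and 0.5%. Recompute the control and pessary rates for the composite in Outcome measures, and restate the power for 660 women with the correlation adjustment shown. If the 77%, 35% and 12% already refer to the severe definition, correct the Background wording instead.

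The pooled, arm-blind event rate at the planned interim after 300 women can serve as a check against the planned average of (7.2% + 3.9%)/2 = 5.55%. It is a coarse check. Even with outcomes on all 600 children, the 95% margin at correlation 0.6 is 1.96×√(0.0555×0.9445×1.6/600), about 2.3 percentage points. A low pooled rate could also reflect a larger treatment effect.

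The cost is a recalculation and possibly a less favourable stated power. This correction needs no extra patients and no change of endpoint.

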## Methods/Design

### Aims

We will use a randomised trial (the ProTwin-trial: Pessaries in multiple pregnancy as a prevention of preterm birth: the ProTwin Trial) to assess the effect of a cervical pessary on neonatal outcome.

The study is set in the Dutch Obstetric Research Consortium, a collaboration of obstetric practices in the Netherlands. Approximately 50 clinics, including academic hospitals, non-academic teaching hospitals and non-teaching hospitals will participate in this trial.

To conduct this trial we got approval from the Medical Ethics Committee, Academic Medical Centre, Amsterdam, The Netherlands (MEC O9/1O7).

### Participants

All women presenting with a multiple pregnancy between 12 and 19 weeks of gestation are eligible for the study. We propose to also include women with monochorionic pregnancies as well as women with a triplet pregnancy or women with a previous preterm birth. Women with multiple pregnancies in which at least one of the foetuses has major congenital anomalies known at study entry will not be included. Gestational age will be determined from the menstrual history and confirmed from the measurement of foetal crown-rump length (of the bigger twin) at a first-trimester scan.

### Procedures, recruitment, randomisation and collection of baseline data

All eligible women who present at one of the participating clinics will be referred to an obstetrician or a specifically appointed research nurse/midwife for counselling. They will receive an information sheet and, where possible, are given two weeks time to reflect on participation.

Once a patient has given informed consent, and the patient data have been entered in a web-based database, randomisation will be done over the internet.

Randomisation will be stratified for centre, parity (previous vaginal delivery or not), chorionicity (multichorial versus monochorial) and number of multiples (twin or higher order gestation).

We will apply block randomisation with a variable block size and a minimalisation procedure. The pessaries will be packaged according to the randomisation sequence at the central consortium office in Amsterdam, the Netherlands. Randomisation will be 1:1 for cervical pessary versus no treatment.

The study will not be blinded.

Baseline demographic, past obstetric and medical histories will be recorded for all women. Cervical length will be measured by transvaginal ultrasound at the time of randomisation or at the next visit.

### Intervention

Eligible women will be randomly allocated to receive either a cervical pessary (Arabin pessary) or no intervention. The cervical pessary will be placed in situ at 16 to 20 weeks, and will stay in situ up to 36 weeks gestation or until delivery, whatever comes first.

All women participating will have a transvaginal measurement for cervical length between a gestational age of 18 to 22 weeks. Next to this research intervention cases are treated according to the local protocol in the participating clinics and other interventions i.e. tocolysis and corticosteroids in case of a threatened preterm birth can be carried out as usual. Furthermore no extra interventions will be needed. The use of progesterone is allowed, but this will mainly depend on the outcome of our current AMPHIA study[10].

### Outcome measures

The main outcome parameter is the composite morbidity rate of children in the two groups. This composite morbidity rate contains the following variables: periventricular leukomalacia (PVL), severe Respiratory Distress Syndrome (RDS), Broncho Pulmonal Dysplasia (BPD), Intraventricular Haemorrhage II B or worse, Necrotizing Enterocolitis (NEC), proven sepsis and death before discharge from the nursery 24. They will be measured until 6 weeks after the expected term date of delivery.

Secondary outcome measures are time to delivery, preterm birth rate before 32 and 37 weeks, days of admission in neonatal intensive care unit, maternal morbidity, maternal admission days for preterm labour and costs. At present, a longer follow-up is not planned.

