### Follow up of women and infants

All details of delivery, maternal assessments and admittance during pregnancy are recorded in the case record form that is accessible through the website. In case of admittance of one or more children to the neonatal intensive care unit, details of this admittance are also recorded. The main outcome parameter, a composite neonatal mortality and morbidity, will be measured until 6 weeks after the expected term date of delivery.

Long-term follow up of children is desirable, but is depending on future funding

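### The death component of the primary outcome is defined inconsistently, and the Outcome measures wording leaves stillbirth and early loss after randomisation uncounted

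*Protocol article*

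**What the plan says.** The protocol article describes the death part of its primary outcome in four places:

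- Abstract, Methods/Design: "The primary outcome is composite bad neonatal condition (perinatal death or severe morbidity".
- Background, where bad neonatal outcome is introduced: "necrotizing enterocolitis (NEC), sepsis and death before discharge".
- Outcome measures, the operative list: "The main outcome parameter is the composite morbidity rate of children in the two groups", with the components ending in "proven sepsis and death before discharge from the nursery".
- Follow up of women and infants: "The main outcome parameter, a composite neonatal mortality and morbidity, will be measured until 6 weeks after the expected term date of delivery".

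On timing, Participants says "All women presenting with a multiple pregnancy between 12 and 19 weeks of gestation are eligible for the study" and Intervention says "The cervical pessary will be placed in situ at 16 to 20 weeks". Data analysis makes intention to treat the first analysis. No section defines perinatal death, mentions stillbirth, miscarriage or fetal loss, or says how such events count.

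**The concern.** Perinatal death, as ordinarily used, includes stillbirth. Death before leaving the nursery, and neonatal mortality, presuppose a child born alive. These are different events, and the article does not say which one governs.

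The difference matters here because the intervention aims to change when delivery happens. With placement at 16 to 20 weeks, a woman carries the pessary for 4 to 8 weeks before 24 weeks (24 − 20 and 24 − 16). Delivery before viability and stillbirth are therefore events after randomisation that the pessary could make more or less frequent. If such fetuses are neither events nor in the denominator, the two arms are compared among survivors to live birth. A pessary that turned early losses into live births with morbidity would look worse than it is, and one that did the reverse would look better. The trial is not blinded, so the choice should not be left until outcomes by arm can be seen.

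**Working it through.** **1. The wordings side by side**

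| Section | Term for death | Stillbirth counted? | Loss before viability counted? |
|---|---|---|---|
| Abstract | perinatal death | ordinarily yes; term not defined | unclear |
| Background | death before discharge | not on a literal reading | not on a literal reading |
| Outcome measures | death before nursery discharge | not on a literal reading | not on a literal reading |
| Follow up | neonatal mortality | not on a literal reading | not on a literal reading |

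The Abstract wording would not settle the matter alone, since an undefined perinatal period may start after some of the losses in question.

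**2. The plan's own rates (Sample size)**

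- Control: 1.8%×77% + 5.4%×35% + 7.2%×12% + 35.6%×8% + 50%×0.5% = 7.24%, stated as 7.2%.
- Pessary: 0.9%×77% + 2.7%×35% + 3.6%×12% + 17.8%×8% + 75%×0.5% = 3.87%, stated as 3.9%.

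Both reproduce. The delivery probabilities sum to 100% in each arm, and the earliest band in the Background is 24–27 weeks, so the planning model allots nothing to earlier loss. The planned relative risk is 3.9/7.2 = 0.54 and the planned difference is 3.3 points. With two children per woman, 330 women give 660 children per arm and 0.072×660 + 0.039×660 ≈ 73 expected events.

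**3. What the definition does to the relative risk**

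The documents give no rate of stillbirth or early loss. The loss rates k below are assumptions, and the planning rates p are taken to apply to liveborn children. The rate with losses counted, over all fetuses, is k + (1 − k)p.

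| Assumed loss, control / pessary | Composite with losses, control / pessary | Relative risk |
|---|---|---|
| 0 / 0 | 7.20% / 3.90% | 0.54 |
| 2% / 2% | 9.06% / 5.82% | 0.64 |
| 3% / 1.5% | 9.98% / 5.34% | 0.54 |
| 1.5% / 3% | 8.59% / 6.78% | 0.79 |

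For the second row: 0.02 + 0.98×0.072 = 0.0906; 0.02 + 0.98×0.039 = 0.0582; ratio 0.64. A liveborn-only analysis would show 0.54 in every row.

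On the difference scale, an uncounted imbalance of 0.5 to 1 point (again an assumption) is about 3 to 7 children per arm of 660, or 0.5/3.3 = 15% to 1/3.3 = 30% of the target difference.

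**4. What counting losses does to planning**

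Children per arm, with p̄ the mean of the two rates: [1.96√(2p̄(1−p̄)) + 0.842√(p₁(1−p₁)+p₂(1−p₂))]² / (p₁−p₂)². For 7.2% v 3.9% this gives 755. Women per arm = 755 × (1 + 0.6)/2 = 604. The stated 330 is not reproduced from the stated inputs. That is a separate matter, and this point does not depend on it; 604 serves only as the reference below.

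| Assumed control loss | Equal loss in both arms: women per arm (power at 330) | Loss reduced in proportion to the outcome: women per arm (power at 330) |
|---|---|---|
| 0 | 604 (54%) | 604 (54%) |
| 1% | 714 (48%) | 526 (60%) |
| 2% | 827 (42.5%) | 465 (66%) |
| 3% | 941 (38%) | 416 (70%) |
| 5% | 1178 (32%) | 342 (79%) |

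Equal losses use k + (1 − k)p in both arms. Proportional losses add k to the control rate and k×3.9/7.2 to the pessary rate. The correlation is held at 0.6 throughout.

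**The case against.** The strongest reply is that exclusion is inferred. Outcome measures does not use the word liveborn, does not define children and states no exclusion. The analysis is by intention to treat, delivery details are recorded for all women, and the full protocol, which is not shown, may say how stillbirths count. This stands against any claim that the plan excludes these fetuses. It does not remove the conflict: an article may leave detail elsewhere, but here it gives its primary outcome incompatible death terms, and any fuller text has to overrule one of them.

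Several stronger readings are tempting and are not supported:

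- **That an imbalance in losses would go unseen.** Time to delivery and birth before 32 weeks are secondary outcomes, so early loss of a whole pregnancy would show there, though not as a death. What could stay hidden is mainly the death of one fetus with the pregnancy continuing, or a stillbirth without early delivery.
- **That the Background figure proves deaths are missing.** It says "about 8% of the multiple pregnancies will result in the death of at least one child". The composite per pregnancy at correlation 0.6 is 2×0.072 − (0.072² + 0.6×0.072×0.928) = 9.87%. But 8% is the smaller number, so the composite could contain every death, and the 8% has no stated time window.
- **That the planning rates belong to a milder composite,** because the Background list does not grade respiratory distress, haemorrhage or sepsis as Outcome measures does. That list may be shorthand, and the sources of the rates are not at hand.
- **That the planning bands define the analysis population.** Starting at 24 weeks may be only a simplification for the sample size.
- **That every woman is randomised at 12 to 19 weeks.** That is the window for presenting and being eligible; randomisation may come later.

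A further objection stands in full: counting all losses is not free. Losses that the pessary does not affect dilute the relative effect and raise the sample size.

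**Conclusion.** The point holds as an inconsistency in the primary endpoint. The Abstract, Outcome measures and Follow up sections name different death events. The operative list, read literally, does not count stillbirth or pre-viable loss after randomisation, and it leaves the denominator unclear. Conditioning on live birth is a consequence if those fetuses are left out; the article does not state that they are.

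The size cannot be fixed from the document. Under assumed losses of 1.5% to 3% per arm, the relative risk with losses counted runs from 0.54 to 0.79, against 0.54 among live births. An imbalance of 0.5 to 1 point would be 15% to 30% of the target difference. These figures illustrate sensitivity to the definition and do not predict the result. They rest on the assumed loss rates, two children per woman, and the planning rates applying to liveborn children.

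**What to change.** Use one definition in the Abstract, Background, Outcome measures and Follow up sections. It should explicitly count stillbirth and fetal loss after randomisation, together with death before discharge (up to 6 weeks after the term date), alongside the listed morbidities. State the denominator as all fetuses of randomised women, analysed in the randomised arm. Report a liveborn-only version as a sensitivity analysis. Settle this before outcomes are looked at by arm, including for the interim analysis after 300 women.

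Data collection should change little, because delivery details are already recorded for all women; the case record form must also capture the death of one fetus in a continuing pregnancy. The real cost is in planning. If the pessary does not affect these losses, the relative effect is diluted (0.54 to about 0.64 at an assumed 2% in each arm) and power falls. If it reduces them in proportion, power rises. The planning rates and stated power should therefore be restated for the chosen definition, with the assumed loss rate given.
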